### Statistical Considerations

Both primary and all secondary endpoints are displayed in Appendix C.

As this study has two primary endpoints, the Hochberg extension of the Bonferroni method for multiple comparisons will be used to test for statistical significance with an overall type I error rate less than or equal to 0.05 [16]. The statistical comparisons of the treatment arms with respect to the primary and secondary endpoints are performed using the independent-samples T-test, or Fisher's exact probability test in case of binary endpoints. All p-values are 2-sided. For clinical outcomes such as the incidence of major adverse cardiac events, Kaplan-Meier curves displaying the pattern of events over the four-month and one-year follow-up period are constructed. Statistical significance and 95-% confidence intervals are calculated using Cox' proportional hazards model.

The trial is powered to detect differences between the two groups in cMRI assessed LVEF and LVEDV at four months after STEMI. With 2 × 150 randomized patients, this trial has an 80% power to detect absolute differences of 4% in LVEF and 15 mL in LVEDV in favor of PCI of the CTO with a one-sided alpha of 5%. For this calculation we have assumed that PCI of a CTO is successful in 80% of cases. The mean global ejection fraction in patients with an untreated CTO is assumed to be 36% against 40% in patients with successful CTO treatment with a common standard deviation of 12%. Consequently, the expected global ejection fraction is 40% (0.8 × 41% + 0.2 × 36%) in patients randomized to CTO treatment against 36% in patients randomized to standard medical treatment. The calculation for the second primary endpoint is based on the assumption of a net mean LVEDV of 185 ml for patients randomized to CTO treatment and of 200 ml for patients randomized to standard medical treatment. The standard deviation for LVEDV was assumed to be 45 ml. Patients who have deceased before primary endpoint measurement will be attributed the lowest LVEF and the largest LVEDV measured in the whole study cohort. The primary endpoint will be analyzed on an intention-to-treat basis.

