#### Other Secondary Endpoints

Measured by cardiac magnetic resonance imaging at 4 months:

- Left ventricular end-systolic volume - Left ventricular segmental wall thickening

- Left ventricular mass - Infarct size (by late contrast enhancement)

N Terminal - pro Brain Natriuretic Peptide (at 4 months and 1 year, relative to baseline)

Heart rate-adjusted QT (QTc) duration measured by resting electrocardiography (at 4 months and 1 year, relative to baseline)

Quantitative Coronary Angiography of the treated chronic total occlusions:

- in-stent and in-segment late luminal loss at 12 months

- in-stent and in-segment minimal luminal diameter

- in-stent and in-segment binary restenosis rate

Repeat Hospitalization for cardiac causes at 30 days, 4 months, and 1, 2, 3, 4, and 5 years

Presence of clinically overt heart failure at 30 days, 4 months, and 1, 2, 3, 4, and 5 years

Implantation of implantable cardioverter-defibrillator devices

Functional Class: NYHA classification at 30 days, 4 months, and 1, 2, 3, 4, and 5 years

*Excluding the initial percutaneous coronary intervention of the chronic total occlusion when randomly

assigned to this treatment arm. MRI: Magnetic resonance imaging NYHA: New York Heart Association

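### The protocol assigns NT-proBNP relative to baseline an unadjusted t-test on an undefined scale; log-scale ANCOVA on baseline would be more efficient at almost no cost.

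*Protocol article*

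**What the plan says.** The Statistical Considerations section of the protocol article refers the reader to Appendix C for all endpoints. On how the two groups are compared, it says that analyses "with respect to the primary and secondary endpoints are performed using the independent-samples T-test"; where an endpoint is binary, Fisher's exact test takes its place. It adds "All p-values are 2-sided". The one exception is for clinical outcomes such as major adverse cardiac events, which get Kaplan-Meier curves; for these, "Statistical significance and 95-% confidence intervals are calculated using Cox' proportional hazards model".

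Appendix C, under Other Secondary Endpoints, lists "N Terminal - pro Brain Natriuretic Peptide (at 4 months and 1 year, relative to baseline" and, further down, "Functional Class: NYHA classification at 30 days, 4 months, and 1, 2, 3, 4, and 5 years". Neither is binary as listed, and neither is a time to an event.

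The article names no rank test, transformation, ordinal method or baseline-adjusted model. It does not say whether NT-proBNP relative to baseline means a difference, a ratio or a log-ratio.

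**The concern.** A method is named here, so the point is about what the text states and not about an omission. For NT-proBNP the named method compares two means without using baseline as a covariate, and the quantity averaged is left open.

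Two features make this inefficient. First, a natriuretic peptide measured after an infarction is likely to be right-skewed, so on the raw scale a few large values dominate the variance. Second, subtracting or dividing by baseline carries all of the baseline noise into the outcome, whereas regression on baseline removes only the part that predicts follow-up.

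What is at stake is the chance of detecting an effect on a secondary blood marker related to the remodelling hypothesis in the article's Discussion. The primary endpoints and the type I error are not affected. Because the scale is open, the same sentence also allows analyses of very different sensitivity.

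**Working it through.** **The plan's own figure.** There is none for NT-proBNP. The only power statement, "With 2 × 150 randomized patients, this trial has an 80% power to detect absolute differences of 4% in LVEF and 15 mL in LVEDV", concerns the primary endpoints. Only its 150 per arm is used here. Fewer patients with paired samples would lower power for every method.

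**Inputs.**
- From the article: 150 per arm, two-sided tests (5% level used here), unadjusted t-test.
- Assumed, because the documents give nothing: bivariate log-normal NT-proBNP; log-SD σ of 0.8 to 1.2 (0.5 as a mild case); log-scale correlation ρ of 0.4 to 0.6; geometric mean ratio 0.75; baseline equal to or twice control follow-up.

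**Step 1: log-scale methods by formula.** Power is Φ(|ln 0.75| / (SD × √(2/150)) − 1.96). Since 0.2877 / 0.11547 = 2.491, this is Φ(2.491/SD − 1.96).
- t-test on log-ratio: SD = σ√(2 − 2ρ).
- Log ANCOVA: SD = σ√(1 − ρ²).

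| σ, ρ | log-ratio SD | power | ANCOVA SD | power |
|---|---|---|---|---|
| 0.8, 0.6 | 0.716 | 94% | 0.640 | 97% |
| 0.8, 0.4 | 0.876 | 81% | 0.733 | 92% |
| 1.0, 0.6 | 0.894 | 80% | 0.800 | 88% |
| 1.2, 0.6 | 1.073 | 64% | 0.960 | 74% |
| 1.2, 0.4 | 1.315 | 47% | 1.100 | 62% |

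The variance ratio of ANCOVA to log-ratio is (1 − ρ²)/(2 − 2ρ) = (1 + ρ)/2. That is 0.7 at ρ = 0.4 and 0.8 at ρ = 0.6. ANCOVA therefore gains on the log-ratio at any correlation below 1, whatever σ is.

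**Step 2: raw scales, one case by formula (σ = 1.0, ρ = 0.6).**
- *Ratio.* The ratio is log-normal with log-variance 0.894² = 0.8, so its coefficient of variation is √(e^0.8 − 1) = 1.107. With means 1 and 0.75, SE = 1.107 × √((1 + 0.5625)/150) = 0.113. Then 0.25/0.113 = 2.21, and power is Φ(0.25) = 60%.
- *Raw change, baseline mean 2, control follow-up mean 1.* Use e^1 − 1 = 1.718 and e^0.6 − 1 = 0.822. Control variance = 1.718 + 4(1.718) − 4(0.822) = 5.30. Treated variance = 0.5625(1.718) + 4(1.718) − 3(0.822) = 5.37. SE = √(10.67/150) = 0.267. Then 0.25/0.267 = 0.94, and power is Φ(−1.02) = 15%.
- *Raw change, baseline mean 1.* The variances are 2(1.718) − 2(0.822) = 1.79 and 0.5625(1.718) + 1.718 − 1.5(0.822) = 1.45. SE = √(3.24/150) = 0.147. Then 0.25/0.147 = 1.70, and power is Φ(−0.26) = 40%.

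**Step 3: simulation.** The normal approximation is rough for skewed data, so power was also simulated (3,000 to 4,000 runs per setting for the table's columns; repeat runs agree within about two points). Results at ρ = 0.6:

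| Method | σ = 0.8 | σ = 1.0 | σ = 1.2 |
|---|---|---|---|
| t, raw change, baseline twice follow-up | 27% | 18% | 11% |
| t, raw change, baseline equal | 71% | 43% | 26% |
| t, ratio | 86% | 62% | 42% |
| t, log-ratio | 94% | 79% | 62% |
| log ANCOVA | 97% | 87% | 73% |

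With ρ = 0.4 included, the full ranges are 10-71% (raw change), 24-86% (ratio), 45-94% (log-ratio) and 60-97% (ANCOVA). At σ = 0.5 and ρ = 0.6, the ratio, log-ratio and ANCOVA all reach about 100%; raw change with baseline twice follow-up reaches 67%.

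**Step 4: type I error.** With no effect and σ of 1.0 and 1.5, the t-test rejects in 4.9% and 3.5% of runs on raw change, and in 4.5% and 3.8% on the ratio. It is valid, if slightly conservative under strong skew.

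**Step 5: NYHA.** Under three assumed class distributions and a common odds ratio of 1.8, power is 69%, 55% and 77% for the t-test against 73%, 59% and 77% for Wilcoxon. The loss is about 1 to 4 points, with t-test type I error of 4.4-5.2%.

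**The case against.** The strongest reply is that this is a design article. Transformations and covariates for secondary endpoints usually belong in the analysis plan, and a log-ratio followed by a t-test would comply with the text. The trial is powered only for LVEF and LVEDV, and the test is valid. Most of this stands, and it keeps the point minor. It does not remove it: the article names a test for the secondary endpoints, and even the most favourable compliant reading, the log-ratio, loses power to ANCOVA.

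Three stronger readings are tempting, and the documents support none of them.
- A reader might infer that the plan leaves NT-proBNP with only 11-27% power, so that a real effect would usually be missed. Those figures need both raw change, which the article does not specify, and an assumed general fall from baseline. Without the fall, raw change gives 71/43/26% at log-SD 0.8/1.0/1.2.
- A reader might infer that every non-binary secondary endpoint is affected. The same section assigns clinical outcomes to a Cox model.
- A reader might infer serious harm to NYHA class, for example 31% power for Fisher's test on class III/IV. The article states no such split. Under the same assumed distribution, Fisher's test on class II or above gives 64%, against 66% for the t-test and 70% for Wilcoxon.

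**Conclusion.** The point holds as a minor one. For NT-proBNP relative to baseline, the article fixes an unadjusted t-test on an undefined scale. This is valid but less efficient than log-scale ANCOVA.

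The advantage over the log-ratio needs only a correlation below 1 and similar log-scale spread at the two times: the variance falls by 20-30% at correlations of 0.6 to 0.4. The larger losses on the ratio and raw change depend on the assumed skewness and, for raw change, on the fall from baseline. They range from negligible to most of the power. The documents give no NT-proBNP data with which to narrow that range.

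For NYHA class, the issue is mainly that a mean class is hard to interpret. It is not a main point.

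**What to change.** Add one sentence to Statistical Considerations: log NT-proBNP at 4 months and at 1 year is analysed by ANCOVA with treatment arm and log baseline as covariates, and reported as a geometric mean ratio with 95% confidence interval. This also settles the scale.

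It needs no extra patients or measurements, because the endpoint already requires a baseline value. The small downside is that the effect is expressed as a ratio and not as an absolute difference.

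Optionally, analyse NYHA over all four classes by the Wilcoxon rank-sum test or proportional-odds regression, mainly for interpretability.

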### Cardiac Magnetic Resonance Imaging

After written informed consent, baseline cMRI is recommended to be performed at least 48 hours after the primary PCI but before the patient is randomly assigned to one of the treatment arms. All patients undergo cMRI at four-month follow-up to assess the primary endpoints of this trial. Patients are studied on a clinical 1.5-Tesla scanner using a 4-element phased array cardiac receiver coil. For functional imaging, electrocardiogram-gated cine steady-state, free-precession magnetic resonance images are obtained during repeated breath holds in the 3 standard long-axis views (4 -, 3- and 2-chamber view). Additional short-axis slices are acquired, covering the entire left ventricle from base to apex, to examine regional and global left ventricular function. Late contrast-enhanced (LCE) images are acquired 10 minutes after administration of a gadolinium-based contrast agent with an inversion recovery, gradient-echo pulse sequence to identify the location and extent of myocardial infarction. The data are obtained with slice locations identical to the functional images. All MRI images are sent to an independent core laboratory for quality control and blinded central analysis. On the short axis cine slices, the endocardial and epicardial borders are outlined manually in end-diastolic and end-systolic images, excluding trabeculae and papillary muscles. Assessment of global left ventricular function is obtained by calculating left ventricular volumes, mass, and ejection fraction using the summation of slice method multiplied by slice distance.

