### Primary Endpoints

The two primary endpoints of this trial are differences between the two treatment arms in left ventricular ejection fraction (LVEF) and left ventricular end-diastolic volume (LVEDV), assessed by cMRI at four months after primary PCI for STEMI, Appendix C.

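### The primary t-test makes no use of the baseline cMRI that the protocol recommends before randomization; a baseline-adjusted analysis would gain precision without new data

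*Protocol article*

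**What the plan says.** The protocol article's Statistical Considerations section fixes the method: comparisons between the arms, for primary and secondary endpoints alike, are "performed using the independent-samples T-test". Binary endpoints go to Fisher's exact test. All p-values are two-sided, and Hochberg's procedure is applied across the two primary endpoints at an overall 0.05. No baseline covariate is mentioned there or elsewhere in the article.

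The Primary Endpoints section defines both endpoints as between-arm differences, "assessed by cMRI at four months after primary PCI for STEMI". They are not changes from baseline.

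The Cardiac Magnetic Resonance Imaging section treats the two scans differently:
- Before treatment assignment, "baseline cMRI is recommended to be performed at least 48 hours after the primary PCI but before the patient is randomly assigned".
- At follow-up, "All patients undergo cMRI at four-month follow-up to assess the primary endpoints of this trial".

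Images go to a core laboratory for blinded reading. On what is derived from them, the section says "Assessment of global left ventricular function is obtained by calculating left ventricular volumes, mass, and ejection fraction". A patient with a baseline scan therefore has a baseline LVEF and a baseline LVEDV.

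**The concern.** A pre-randomization measurement of the endpoint itself is the natural covariate in a trial of this kind. The protocol arranges for it and then gives it no role in the primary comparison. With a continuous endpoint, adjusting for baseline in a linear model estimates the same four-month mean difference as the t-test. It also removes chance baseline imbalance and reduces the variance of the estimate whenever baseline and follow-up are correlated.

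The margin matters here. Under Hochberg, an endpoint is tested at 0.05 only if the other also reaches 0.05; otherwise it must reach 0.025. At that stricter level the unadjusted test falls below the planned 80% power. Precision from scans that are already recommended is the cheapest way to recover some of it.

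**Working it through.** **Inputs from Statistical Considerations.** The sample size is "With 2 × 150 randomized patients". The difference is 4 points in LVEF with SD 12, and 15 mL in LVEDV with SD 45. The standardized effect is 4/12 = 15/45 = 1/3, so every figure below applies to either endpoint.

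**The plan's own figure.** For a t-test with n per arm, the noncentrality is (1/3)/√(2/n). At n = 150 this is 0.3333/0.1155 = 2.887. Noncentral-t power is:
- one-sided 0.05, the stated planning level: 89.2%, not the stated 80%
- two-sided 0.05: 82.1%
- two-sided 0.025: 73.7%

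The mismatch with 80% is a separate matter. The two-sided values are the right comparators here because the analysis is two-sided.

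**Assumed inputs.** The document gives neither r nor q. I take r from 0.3 to 0.7 and q from 0.5 to 1.

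**Effect of adjustment.** If all patients stay in the model, with a missing baseline imputed and flagged, the variance of the treatment effect is multiplied by about 1 − q·r². The noncentrality becomes 2.887/√(1 − q·r²).

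| r | q | 1 − q·r² | Noncentrality | Power, two-sided 0.05 | Power, two-sided 0.025 |
|---|---|---|---|---|---|
| unadjusted | – | 1 | 2.887 | 82.1% | 73.7% |
| 0.3 | 0.5 | 0.955 | 2.954 | 83.8% | 75.8% |
| 0.5 | 0.5 | 0.875 | 3.086 | 86.8% | 79.7% |
| 0.5 | 1 | 0.75 | 3.333 | 91.3% | 85.9% |
| 0.7 | 1 | 0.51 | 4.042 | 98.1% | 96.3% |

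**Why patients without a baseline scan must be kept.** A complete-case ANCOVA has variance proportional to (1 − r²)/q. It does worse than the t-test on everyone whenever q < 1 − r². At r = 0.5 the break-even is q = 0.75. With q = 0.7 and r = 0.5, the normal approximation gives 79.6% for complete-case ANCOVA at two-sided 0.05, against 82.3% for the unadjusted test on all patients.

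**The case against.** The strongest reply is that nothing here is wrong. Under 1:1 randomization the t-test is valid and unbiased for the endpoint as defined, and the sample size uses raw SDs that match it. This stands: a reader might infer that the planned test is biased or invalid, and the document does not support that. Nor is the power claim built on an adjustment that is then left out.

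A second reply is that an article condenses the plan and that covariates are often left to an SAP. That would carry weight if the article were silent. It names the test for the primary endpoints, so the choice is stated and open to comment.

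Third, a reader might infer that baseline LVEF and LVEDV are available for everyone and the precision is already paid for. The document does not say so. The baseline scan is recommended, whereas the four-month scan is for all patients, so coverage is unknown. No correlation is given either, so a claim that baseline is the strongest predictor, or that the gain must be large, has no support in the text. At r = 0.3 and half coverage the gain is about two points of power.

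Two further features would probably weaken the correlation, and the table ignores both. Deaths before the endpoint receive the lowest LVEF and largest LVEDV in the cohort. The Follow-up section also allows SPECT or echocardiography at four months when a contraindication to cMRI has arisen.

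Finally, the same t-test rule covers secondary endpoints such as "N Terminal - pro Brain Natriuretic Peptide (at 4 months and 1 year, relative to baseline" and the QTc measure. It is tempting to read this as a t-test on raw change, but the wording does not settle whether change, ratio or an adjusted value is meant. That point is secondary and the conclusion does not rest on it.

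**Conclusion.** The point holds as an efficiency recommendation. The stated primary analysis leaves out a covariate that the protocol itself recommends collecting before randomization, and using it would leave the estimand and the Hochberg procedure unchanged.

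Over the assumed range the gain runs from 1.7 to 16.0 percentage points of power at two-sided 0.05 (83.8 − 82.1 and 98.1 − 82.1). At two-sided 0.025 it runs from 2.1 to 22.6 points (75.8 − 73.7 and 96.3 − 73.7). The upper ends need a baseline scan in every patient and r = 0.7, and should not be quoted as the expected gain. All figures take the stated effects and SDs at face value, assume an endpoint value for all 300 patients, and leave out the worst-value rule for deaths.

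**What to change.** Make the primary analysis of each endpoint an ANCOVA of the four-month value on treatment arm and the baseline value of the same measure, keeping the two-sided Hochberg procedure as it is.

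State the rule for a missing baseline in advance: impute it without regard to arm (for example, the overall baseline mean), add a missing-baseline indicator, and keep every randomized patient in the model. Use as covariate only scans made before randomization, and treat a later one as missing. Do not use a complete-case ANCOVA as the primary analysis.

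Keep the independent-samples t-test as a sensitivity analysis. Rank ANCOVA is not part of this change, because it would no longer estimate a mean difference in LVEF points or mL.

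The cost is a few sentences in the plan and minor programming, with no new patients or scans. It should be settled before unblinding, since adjustment chosen after the results are seen is open to challenge.

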### Follow-up

All patients visit the outpatient clinic at 30 days, four months, and twelve months after primary PCI. Thereafter, patients will be followed-up by means of a telephone call at two, three, four, and five years. During all three follow-up outpatient clinic visits, clinical evaluation with a 12-lead electrocardiogram and an inventory of adverse events is obtained. Adverse events included in this inventory are cardiac and non-cardiac death, stent thrombosis according to the definition of the Academic Research Consortium (ARC)[15] myocardial re-infarction, all cardiac surgery, implantation of an implantable cardioverter-defibrillator device, clinically overt heart failure, repeat coronary angiography and repeat PCI, hospital admission for angina, stroke, and severe bleeding events.

At four months, cMRI is performed in all patients along with routine laboratory measurements and exercise testing. If a contraindication for cMRI has risen because of altered patient characteristics after inclusion, the protocol permits single positron emission computed tomography (SPECT) as a secondary and echocardiography as a tertiary modality for endpoint assessment.

Scheduling of repeat angiography is at the discretion of the treating physician. Repeat angiography is preferably performed at one year after randomization in all patients.

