### Safety and Other Secondary Endpoints

Safety will be determined by the assessment of Major Adverse Coronary Events (MACE) defined as cardiac death, peri-procedural myocardial infarction, myocardial infarction or any repeat coronary intervention at 30 days, 4 months and 1, 2, 3, 4, 5 years. Furthermore, safety is also determined by the occurrence of stent thrombosis. All safety endpoints are defined in accordance with the ARC [15]. The trial will be monitored by a Data and Safety Monitoring Board (DSMB) and the trial will be discontinued in case of safety concerns.

All other secondary endpoints are displayed in Appendix C.

A pre-specified subgroup analysis will be performed in which the primary outcome, Major Adverse Coronary Events (MACE) and suitable other secondary endpoints will be stratified according to the presence of non-CTO co-existing lesions.

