### PCI of a CTO: higher risk of restenosis

Percutaneous recanalization of a CTO amenable to PCI treatment can be performed with a success rate of 70-80%, but is associated with a higher rate of restenosis compared to PCI of non-occluded vessels. Although coronary stenting has been shown to be superior to conventional balloon angioplasty, restenosis rates remain relatively high. When compared to bare metal stents, drug eluting stents (DES) are effective in decreasing the need for repeat intervention in successfully treated CTO patients.[27] However, there have been concerns about long-term delay of arterial healing as a consequence of both Sirolimus eluting stent (SES) and Paclitaxel eluting stent (PES) placement and the associated risk of late stent thrombosis. Both preclinical and clinical data for a second-generation DES, the EES, are encouraging in terms of arterial healing and low restenosis rates. The EES showed superior endothelialization compared with the PES, SES and Zotarolimus-eluting stent at 14 days after stent implantation.[28] This suggests a superior safety profile for the EES, as shown in the one-year results of the SPIRIT IV trial, randomizing 3687 patients in a 2:1 fashion to either the EES or the PES for treatment of patients with de novo coronary artery disease with a maximum of 3 lesions. The SPIRIT IV investigators reported a 0.29% ARC definite or probable stent thrombosis rate in the EES arm, as compared to 1.1% in the PES arm (p = 0.003). Furthermore, the EES performed superior over the PES regarding ischemia-driven target lesion revascularization, (3.9% vs 6.6%, p = 0.0008).[29] Although extensively studied in relatively low-risk lesions, currently data regarding the performance of the EES in CTO's are lacking.

To conclude, no clinical trial to date has investigated the effect of percutaneous recanalization of CTO's on clinical endpoints in any setting. The high case-fatality rates and inferior recovery of LV function after STEMI of patients with a CTO in a non-IRA provide the rationale for the current trial. The ongoing EXPLORE trial is the first randomized clinical trial powered to investigate clinical outcome after percutaneous treatment of a CTO. The Explore trial will determine whether recanalization of a CTO within one week after primary PCI for STEMI results in a better preserved residual left ventricular ejection fraction and reduced end-diastolic volume.

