### Secondary Endpoints

#### Safety Endpoints

Major Adverse Cardiac Events, defined as cardiac death, myocardial infarction or any repeat coronary

intervention* at 30 days, 4 months, and 1, 2, 3, 4, and 5 years

Stent thrombosis, classified as definite, probable or possible

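### Kaplan-Meier curves for the incidence of MACE and similar outcomes slightly overstate that incidence when deaths that are not events are censored; cumulative incidence curves would correct this at almost no cost

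*Protocol article*

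**What the plan says.** Statistical Considerations in the protocol article fixes the display for clinical outcomes: "For clinical outcomes such as the incidence of major adverse cardiac events, Kaplan-Meier curves displaying the pattern of events". The time frame is limited to two horizons, since the curves "over the four-month and one-year follow-up period are constructed". Inference is assigned separately: "Statistical significance and 95-% confidence intervals are calculated using Cox' proportional hazards model". The same section gives Fisher's exact test to binary endpoints.

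MACE is defined under Safety and Other Secondary Endpoints as "cardiac death, peri-procedural myocardial infarction, myocardial infarction or any repeat coronary intervention at 30 days, 4 months and 1, 2, 3, 4, 5 years". Appendix C agrees as to death, in a definition that opens "Major Adverse Cardiac Events, defined as cardiac death, myocardial infarction or any repeat coronary". Only cardiac death is a component in either place. Non-cardiac death is nevertheless collected, according to Follow-up: "Adverse events included in this inventory are cardiac and non-cardiac death".

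Appendix C also lists clinical outcomes that have no death component: cardiac rehospitalization, ICD implantation, and heart failure, worded as "Presence of clinically overt heart failure at 30 days, 4 months, and 1, 2, 3, 4, and 5 years". The Kaplan-Meier sentence does not name them. MACE is given there as an example, so the sentence can extend to them but need not.

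No competing-risk estimator is named, and the article does not say in words that deaths are censored. Its one explicit rule for deaths assigns the worst observed values of the two primary MRI endpoints.

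**The concern.** The sentence names a quantity, incidence, and an estimator, Kaplan-Meier. The two agree only when nothing other than the event can end a patient's risk. A patient who dies of a non-cardiac cause can no longer have a MACE, and a patient who dies of any cause can no longer be admitted with heart failure. Kaplan-Meier has only events and censored observations, so unless the endpoint is redefined these deaths are censored. The estimate then describes a population in which nobody dies of the competing cause, and it is too high for the patients actually randomized.

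Two features of the trial make this worth asking. The Discussion gives as part of the rationale "The high case-fatality rates and inferior recovery of LV function after STEMI of patients with a CTO" in a non-infarct artery, so deaths are expected. It also suggests that opening the occlusion may improve survival, so competing mortality could differ between arms and the overstatement could differ with it. What is at stake is the accuracy of the plotted secondary incidences and of the arm difference read from the curves. The primary MRI comparison is not involved.

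**Working it through.** **No figure of the plan to reproduce.** The article states no event rate, no death rate and no event-based sample size. All rates below are assumptions, shown as ranges. The only input taken from the article is 150 patients per arm.

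**Formulas.** Take constant hazards over one year, with e the net risk of the event (which 1-KM estimates) and m the net risk of competing death.
- Cumulative hazards: L = -ln(1 - e) and K = -ln(1 - m).
- Kaplan-Meier with competing deaths censored: 1-KM = 1 - exp(-L) = e.
- Incidence with death as a competing event: CIF = L/(L + K) × [1 - exp(-(L + K))].
- Overstatement: e - CIF.

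**MACE, where only non-cardiac death competes.** For e = 20%, L = 0.2231. With m = 2%, K = 0.0202, so CIF = 0.2231/0.2433 × (1 - 0.80 × 0.98) = 0.917 × 0.216 = 19.8%.

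| Non-cardiac death | 1-KM | CIF | Overstatement (points) |
|---|---|---|---|
| 0.5% | 20% | 19.95% | 0.05 |
| 1% | 20% | 19.9% | 0.1 |
| 2% | 20% | 19.8% | 0.2 |
| 3% | 20% | 19.7% | 0.3 |
| 4% | 20% | 19.6% | 0.4 |

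**Outcomes with no death component, where any death competes; mortality 10% (K = 0.1054).**
- e = 15%: L = 0.1625; CIF = 0.607 × (1 - 0.85 × 0.90) = 0.607 × 0.235 = 14.3%. Overstatement 0.7 points.
- e = 20%: CIF = 0.679 × (1 - 0.80 × 0.90) = 0.679 × 0.28 = 19.0%. Overstatement 1.0 point.

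Both are about 5% in relative terms. With 5% mortality and e = 20%, CIF is 19.5% and the overstatement is 0.5 points.

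**Which quantity moves with mortality.** A simulation of 400,000 patients with the event hazard fixed at e = 10% gave 1-KM of 10.0% at both 2% and 10% competing mortality. The cumulative incidence fell from 9.95% to 9.5% (9.9% and 9.5% by formula). The Kaplan-Meier curve stays where it is. The true incidence moves, and so does the gap between them.

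**Comparison with sampling error.** The standard error of a difference between two arms of 150 is √(2p(1 - p)/150). That is 3.5 points at p = 10% and 4.6 points at p = 20%. The MACE overstatement is less than a tenth of this, and the largest figure above is roughly a fifth.

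**The case against.** The case for leaving the sentence alone has several good parts.

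- **MACE already includes cardiac death.** It is the only outcome the sentence names, and only non-cardiac death competes with it. The bias is a few tenths of a point and would not be visible on the plot. This stands.
- **The non-fatal outcomes are not named.** They are reached only by reading MACE as an example. Heart failure, listed as present or absent at set times, could equally be analyzed as binary with Fisher's exact test, and a crude proportion with complete follow-up does not have this bias. This stands, so the larger figures are conditional on these outcomes being plotted.
- **The mortality assumption may be high.** The case-fatality remark describes the wider patient group. Appendix B excludes age over 80, persistent hemodynamic instability, cardiac events before randomization and life expectancy under one year. This also stands: 10% is an assumption, and lower mortality shrinks the bias.
- **Inference rests on the Cox model.** Its hazard ratio remains interpretable as cause-specific when competing deaths are censored. This stands.
- **Competing-event rules belong in the SAP.** This stands only in part. Further censoring detail may well be there and its absence here is no fault, but the article does state an estimator for a named quantity, and that pairing can be assessed as written.

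A reader might infer more than the document supports. One inference is that the Kaplan-Meier curves themselves shift with each arm's mortality; with the event hazard fixed they do not. Another is that the bias builds up over five years. Endpoints are listed to five years, but the curves are prescribed only for four months and one year, so five-year figures do not apply.

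**Conclusion.** The point holds as a minor one. Kaplan-Meier is prescribed for the incidence of outcomes that some deaths preclude without being counted. With those deaths censored, 1-KM cannot fall below the true incidence and lies above it whenever competing deaths occur. The size of the overstatement depends on competing mortality in each arm.

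At one year it is about 0.05 to 0.4 points for MACE, and about 0.7 to 1.0 points for the non-fatal outcomes if they are plotted. These sizes rest on constant hazards and on the assumed rates: MACE 20% with 0.5 to 4% non-cardiac death, and non-fatal outcomes of 15 to 20% with 10% mortality. They are below the sampling error of an arm difference. It would go too far to conclude that a significance test, a safety conclusion or either primary endpoint is compromised. The reason to act is that the bias has one direction, does not shrink with more patients, and is very cheap to remove.

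**What to change.** In Statistical Considerations, replace the Kaplan-Meier curves for these outcomes with Aalen-Johansen cumulative incidence curves over the same four-month and one-year periods. For MACE, the competing event is non-cardiac death. For any outcome without a death component that is shown as a curve (heart failure, cardiac rehospitalization, ICD implantation), it is death from any cause. Keep the Cox model and label its result a cause-specific hazard ratio, so that it is not read as a ratio of the plotted incidences.

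The cost is about one sentence of analysis wording. Cardiac and non-cardiac deaths are already in the adverse-event inventory, so no change to data collection, sample size or design is needed. The curves will be a little less familiar to some readers, and the reported incidences slightly lower.
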